### Follow-up

At hospital discharge, the patients will be booked for follow-up after 12 months in the outpatient clinic for abdominal palpation and abdominal CT-scan with intravenous contrast and Valsalva manoeuvre. In addition, the SF-36 questionnaire will be completed at the 3- and 12-month follow-up.

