The method with VAC was initially introduced in damage control trauma surgery and has gained increasing use in the treatment of complicated intra-abdominal infections [21, 31–43]. A systematic review and meta-analysis by Atema et al. in 2015 showed an incidence of 14.6% for enteroatmospheric fistula (EAF) and 48.5% for incisional hernias in the group treated with VAC, where 82% of the population was treated for peritonitis. The mortality varied between 21.5 and 30.0%. The VAC procedure can be applied and modified in several ways. The most common are fascial traction methods (mesh mediated or non-mesh mediated), the applied vacuum pressure and the interval for changes of the VAC [42]. The VAC treatment in the present study will be performed with a non-mesh-mediated fascial traction method and narrowing technique. A retrospective study from our institute using this technique, including 115 patients with secondary peritonitis, found a mortality rate of 17% and EAF of 3.5%; secondary closure was obtained in 92% of the patients [44].

The present study will aim to compare the postoperative results of ROD and VAC in patients with secondary peritonitis by a randomised controlled trial with peritonitis-related complications as the primary outcome; comprehensive complication index (CCI), mortality, quality of life, the development of incisional hernia, and hospital care utility and costs were the secondary outcomes.

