Incisional hernia: full-thickness discontinuity in abdominal wall with bulging of abdominal contents with or without obstruction with disabling concerns interfering with daily activities
Bowel obstruction or herniation due to intra-abdominal adhesions: diagnosis must be confirmed during surgery
Burst abdomen: complete midline or transverse discontinuity in abdominal wall
Abdominal compartment syndrome: intra-abdominal hypertension ≥ 25 mm Hg with tense abdomen and with increasing respiratory failure, renal failure, or both, measured by the urinary bladder pressure method (modified Burch criteria)
Fistula: non-anatomical connection between intestine and cutis, communication between GI tract and external atmosphere or between 2 hollow organs
Intra-abdominal bleeding: only when septic bleeding after index laparotomy or relaparotomy or surgical bleeding after relaparotomy but not after index laparotomy
Intra-abdominal haematoma needing surgical evacuation
Perforation of visceral organ confirmed at surgery
Anastomotic leakage: anastomotic leak on contrast imaging needing surgery or contrast-enhanced computed tomography scan, confirmed at relaparotomy
Ischemia or necrosis of a visceral organ: critically reduced blood flow to an intra-abdominal organ causing tissue loss, confirmed at pathological examination
Enterostomy dysfunction due to prolapse, stenosis, or retraction
Gastric or duodenal ulcer bleeding needing intervention of any type

Reference Table 1: van Ruler O, Mahler CW, Boer KR, Reuland EA, Gooszen HG, Opmeer BC, de Graaf PW, Lamme B, Gerhards MF, Steller EP, van Till JW, de Borgie CJ, Gouma DJ, Reitsma JB, Boermeester MA; Dutch Peritonitis Study Group. Comparison of on-demand vs planned relaparotomy strategy in patients with severe peritonitis: A randomised trial. JAMA. 2007 Aug 22;298(8):865–72. Available from: http://dx.doi.org/10.1001/jama.298.8.865

**Table 2 Tab2:** Health care utility

Length of admission at ICU (Total number of days in a three-month period)
Length of admission at ward (Total number of days in a three-month period)
VAC—Time from index operation to primary closure
Total amount of VAC dressing changes (number of times)
Number of scheduled VAC changes
Number of re-operations with VAC
Number of re-operations
Number of radiologic interventions during admission(s)
Number of computed tomography scans after index operation
Number of days alive outside the ICU in a three-month period

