## Methods

### Study design

A multicentre non-blinded superiority randomised controlled trial on VAC vs. ROD. Danish, as well as other European centres, will be invited to participate. The study protocol adheres to the guidelines determined in Standard Protocol Items: Recommendations for Interventional Trials (SPIRIT) (Additional file 2) [45].

The VACOR study will include two separate studies: VACOR-Main and VACOR-Microdialysis.

All centres must participate in the VACOR-Main study, with only Odense University Hospital participating in the VACOR-Microdialysis study. VACOR-Main will report on all primary and secondary outcomes; in VACOR-Microdialysis, a sub-study of 10 patients from each group will be included. A microdialysis catheter will be placed in the peritoneal cavity, and samples of the peritoneal fluid will be collected every 6th hour to measure the concentration of lactate, glucose, pyruvate, glycerol, cytokines (IL-1b, IL-6, IL-10, TNF-a) and metalloproteins (MMP9 and MMP8). The purpose is to investigate intraperitoneal metabolic changes and inflammatory responses in the two groups.

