#### Data collection and participant timeline

The pre- and perioperative assessment will consist of: baseline data (sex, age, surgery date, height, weight, body mass index, ASA score, WHO performance score, smoking, alcohol consumption, presence of comorbidities, previous abdominal surgeries, and steroid use). Data for surgical findings include aetiology of disease, anatomical location of intestinal perforation, degree of contamination, surgical treatment, method of abdominal wall closure, and suture material used for abdominal wall closure. Postoperative monitoring consists of SOFA, APACHE II, CRP, VAC treatment duration, unplanned VAC change, and the number of laparotomies in the ROD group. A patient record review will be performed at the follow-up after one month, three months, one year, and five years (Fig. 3). All data will be stored in REDCap®, hosted by the Odense Patient data Explorative Network (OPEN).

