#### Sample size and power

With an expected peritonitis-related complications rate of 40% in the ROD group [20] and 25% in the VAC group [42, 44], the desired power of 80%, a significance level of 0.05, and an expected drop-out of 5%, a total of 340 patients should be included.

As the CCI distribution in this group of patients is unknown, we could not perform an explicit sample size calculation for this secondary outcome. A 0.32 standard deviation difference in mean CCI between the two groups could be detected with 80% power with this sample size.

To ensure sufficient recruitment, the study will be multicentre and European. Eight active centres have been included, and two are in process. Randomisation tools along with eligibility criteria are accessible through our website. The workflow and relevant contact details appear on posters at the participating departments. Study progress will be available on the website.

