## Discussion

The VACOR trial addresses several important unanswered clinical questions in the surgical treatment of complicated intra-abdominal infections with special reference to the choice of primary abdominal closure with ROD or the open abdomen with VAC treatment.

In some conditions such as severely complicated peritonitis, second look for ischemia and septic shock, where patients have substantial visceral oedema with high risks of abdominal compartment syndrome, establishing an OA with VAC may be preferred [5, 17, 19, 24]. According to intention-to-treat and per-protocol principles, these patients will be included in the present study. The OA with VAC treatment may have several benefits, including drainage of residual infection, preventing intra-abdominal compartment syndrome, and the timely treatment of complications. The disadvantages are incisional hernia and EAF [23, 42, 44, 51–55]. A recent review of temporary abdominal closure techniques found a higher incidence of EAF in septic than non-septic patients (12.1% vs. 3.7%, respectively) [56]. A large cohort study by Coccolini et al. [57], including 649 patients treated with OA where most patients had peritonitis, could not confirm that peritonitis or temporary abdominal closure with or without negative pressure was related to the incidence of EAF. In systematic reviews with meta-analyses and non-randomised studies it has been shown that VAC is the safest of all temporary abdominal closure techniques [21, 31–43].

In a study including patients with severe secondary peritonitis, patients were randomised to OA with non-resorbable polypropylene mesh versus primary closure with ROD [58]. The study was discontinued at the first interim analysis. The study showed an insignificant higher mortality risk in the OA group of 55% compared to 30% in the ROD group. However, there was a relative risk of 1.83 and an odds ratio of 2.85 in the OA group. Hence, the authors concluded a tendency towards a better outcome in the ROD group.

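### The trial is declared non-blinded without exception, and no masked reading is described for the 12-month hernia outcome, which rests on palpation and CT

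*Protocol article*

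**What the plan says.** The Study design section describes "A multicentre non-blinded superiority randomised controlled trial on VAC vs. ROD" and does not exempt outcome assessors. The Objectives list the 12-month incisional hernia rate as a secondary outcome, judged by clinical examination and CT. The Follow-up section gives the method: "follow-up after 12 months in the outpatient clinic for abdominal palpation and abdominal CT-scan with intravenous contrast and Valsalva manoeuvre". It does not say who examines the patient, who reads the scan or whether either knows the allocation.

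The article also states which way it expects hernia to go. The Background lists incisional hernia among the risks of VAC and cites a meta-analysis with 48.5% hernia after VAC. The Discussion says of open abdomen with VAC: "The disadvantages are incisional hernia and EAF".

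**The concern.** The operation cannot be masked from the surgeon, but a CT reading can be masked without changing treatment. Small fascial defects and bulging on Valsalva are partly matters of judgement, and the article itself sets up a directional expectation for this outcome. If the assessor knows the arm, borderline cases may be called differently in the two arms.

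Randomisation balances the patients, not the way they are assessed a year later. The intention-to-treat analysis, the per-protocol analysis and the multiple imputation all take the recorded hernia status as given, so none of them would detect or remove a differential reading. At stake is the credibility of the trial's comparison on one of the main harms it attributes to VAC.

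**Working it through.** The plan gives no figure for the hernia outcome, so there is none to reproduce. The sample size of 340 is set on the primary outcome and does not change here. The calculation below only shows how sensitive the hernia comparison would be to a differential reading.

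**Inputs**
- Patients per arm: 340 / 2 = 170, assuming equal allocation.
- Assessed at 12 months: assumed 120 per arm. For scale, the Background cites one-year mortality of 29% for on-demand relaparotomy in an earlier trial, and 170 × 0.71 = 120.7. The range tried is 108 to 136 (170 × 0.64 and 170 × 0.80, rounded down).
- True hernia rate, equal in both arms: assumed 35%. The range tried is 20% to 48.5%, the upper end being the cited meta-analysis figure.
- Shift in the recorded rate in one arm from knowing the allocation: assumed 3, 5 or 8 percentage points. The documents support no particular value.

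**Formula**
- Standard error of the difference: SE = √(2 × p × (1 − p) / n) = √(2 × 0.35 × 0.65 / 120) = 0.0616.
- Two-sided rejection probability at 5% with shift d, normal approximation: Φ(d/SE − 1.96) + Φ(−d/SE − 1.96).

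**Results for 120 per arm and 35%**

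| Shift | d/SE | Rejection probability |
|---|---|---|
| 0 | 0 | 5% |
| 3 points | 0.487 | 0.0704 + 0.0072 = 7.8% |
| 5 points | 0.812 | 0.1255 + 0.0028 = 12.8% |
| 8 points | 1.299 | 0.2544 + 0.0006 = 25.5% |

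Over 108 to 136 per arm and 20% to 48.5% hernia, the three shifts give about 7% to 9%, 11% to 18% and 22% to 38%.

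**A second model.** Suppose instead that 5% to 10% of hernia-free VAC patients are wrongly called positive. With p = 30%, 10% false calls and 120 per arm, the recorded VAC rate is 0.30 + 0.70 × 0.10 = 37%, a spurious difference of 7 points. The chance of a significant excess in the VAC arm is then 21%, against a nominal 2.5% in that direction. Over the same ranges of patients and rates, the spurious difference is about 3 to 8 points and that chance is about 6% to 34%.

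Both models assume equal true rates. If VAC really causes more hernias, as the article expects, the same shift would bias the estimated difference by its own size instead of creating a false positive.

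**The case against.** The strongest reply is that the article is silent on this point and silence is not a fault. It condenses a fuller protocol that is not shown, non-blinded may refer only to patients and surgeons, and reader identity and masking logistics are commonly left to the longer document. Part of this stands. A reader might infer that staff who know the arm read the CT, or that no outcome anywhere in the trial is read masked. The article establishes neither. It does declare the design non-blinded without qualification, and it describes the scan down to contrast and Valsalva without mentioning masking. That is enough to ask for a concrete change.

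The reply that the numbers are assumed also stands: the shift is exactly what is unknown, and its direction could go either way. A reader might add that the lead centre has its own published series with this technique ("A retrospective study from our institute using this technique"). That is not evidence of biased reading, since the trial is multicentre and the article openly lists hernia as a drawback of VAC.

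It would also be tempting to extend the point to the primary outcome, because Table 1 qualifies incisional hernia by "with disabling concerns interfering with daily activities". The documents do not support changing that row. It sits under morbidity needing surgical intervention, so surgery is already required and the phrase only narrows it. Removing the phrase would leave the decision to operate, which is unmasked as well. Table 1 is taken from the cited trial that supplied the 40% control rate in the sample size calculation, so altering a component would loosen that link.

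Finally, masked reading cannot be called free. The documents do not cover CT reporting workflow, and a reader who opens the record or earlier scans may learn the arm.

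**Conclusion.** The point holds in limited form. The trial is declared non-blinded with no exception for assessors, and no masked assessment is described for an outcome that rests on palpation and CT and has a stated expected direction. That leaves the hernia comparison open to differential assessment that the planned analyses cannot repair.

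The size is unknown. The rise in the false-positive rate from 5% to about 8% to 25% rests on 120 assessed patients per arm, a 35% hernia rate in both arms and a one-arm shift of 3 to 8 points. It shows sensitivity and is not an estimate of bias in this trial. Hernia is a secondary outcome, so the change is worth making but the primary comparison does not depend on it.

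**What to change.** State in the protocol that the radiologist who would ordinarily read the 12-month CT is not told the allocation, that the arm is left off the request, and that hernia is recorded yes or no against a fixed abdominal-wall-defect definition. Make this masked CT reading the main hernia result and report palpation separately. If masked reading is already planned, saying so and naming the deciding modality is enough. Leave Table 1 unchanged.

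The cost is wording in the protocol and on the CT request. The scan is already planned at 12 months, and no extra reader, visit or patient is needed. There are two small downsides: masking may fail where the reader sees the record or earlier scans, and palpation would no longer decide a case that CT calls negative.

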#### Data collection and participant timeline

The pre- and perioperative assessment will consist of: baseline data (sex, age, surgery date, height, weight, body mass index, ASA score, WHO performance score, smoking, alcohol consumption, presence of comorbidities, previous abdominal surgeries, and steroid use). Data for surgical findings include aetiology of disease, anatomical location of intestinal perforation, degree of contamination, surgical treatment, method of abdominal wall closure, and suture material used for abdominal wall closure. Postoperative monitoring consists of SOFA, APACHE II, CRP, VAC treatment duration, unplanned VAC change, and the number of laparotomies in the ROD group. A patient record review will be performed at the follow-up after one month, three months, one year, and five years (Fig. 3). All data will be stored in REDCap®, hosted by the Odense Patient data Explorative Network (OPEN).

**Fig. 3 Fig3:**
[figure not shown]
Participant timeline

#### Sample size and power

With an expected peritonitis-related complications rate of 40% in the ROD group [20] and 25% in the VAC group [42, 44], the desired power of 80%, a significance level of 0.05, and an expected drop-out of 5%, a total of 340 patients should be included.

As the CCI distribution in this group of patients is unknown, we could not perform an explicit sample size calculation for this secondary outcome. A 0.32 standard deviation difference in mean CCI between the two groups could be detected with 80% power with this sample size.

To ensure sufficient recruitment, the study will be multicentre and European. Eight active centres have been included, and two are in process. Randomisation tools along with eligibility criteria are accessible through our website. The workflow and relevant contact details appear on posters at the participating departments. Study progress will be available on the website.

#### Statistical analysis

Patient characteristics will be summarised with frequencies and proportions (for categorical variables) or with mean values ± standard deviation, median values, quartiles, and minimum and maximum values (for numerical variables). Categorical variables will be compared using a Fisher's exact test and continuous variables with a Wilcoxon rank-sum test.

The primary peritonitis-related complication outcome will be compared between intervention groups by the Chi-square test, reported as relative risk with a 95% CI. The CCI outcome will be compared by linear regression with bootstrapped standard errors reporting the mean difference with 95% confidence intervals.

The main analysis will be performed as a superiority analysis of VAC treatment against primary closure with ROD. In addition, a non-inferiority analysis with a margin of 5% will be reported for peritonitis-related complications as a secondary analysis.

A univariate analysis will be performed on the individual complication types (abscess, leakage, etc.) and complications as a whole (peritonitis-related complications and CCI). Fisher's exact or Chi-square test will be used to compare the treatments depending on the number of observations.

Adjusted analysis by logistic regression will be performed for complications as a whole and the individual complications as an outcome, adjusted for age, performance status, and comorbidity. The above analyses will also be performed as a subgroup analysis where patients with APACHE II score > 10 will be included. This evaluates VAC and ROD in the most seriously ill portion of the patient population.

The hospital healthcare utility and average treatment costs are compared between the treatment groups. The resource use will be reported as the mean difference with 95% confidence intervals (CI) compared by linear regression. In case of deviations from normality assumptions, bootstrapping with 1000 repetitions will be performed. Finally, the proportion of patients who experience radiological, acute operations will be compared by binomial regression estimating relative risk (RR) with 95% CI.

The interim analysis will be performed at 25%, 50%, and 75% of recruited patients on the primary outcome after 30-days to detect significant differences between groups at the earliest possible time, ultimately leading to the termination of the study. We have adjusted our power calculation to the interim analyses using the O'Brien–Fleming method. The study group will have access to the results of the interim analyses and may make the final decision to terminate the study.

All of the above analyses will be performed as both intention-to-treat (patients will be analysed according to their randomisation group) and per-protocol analysis (what actually happened). The main analyses will be performed as complete case analyses. Multiple imputations will impute missing values in a supplementary analysis, including baseline characteristics as predictors.

*P* values < 0.05 will be considered statistically significant. Statistical calculations will be performed using Stata software (version 15, Stata Corp LP, Texas, USA).

In the VACOR-Microdialysis sub-study, the parameters will be compared using descriptive statistics for continuous and discrete variables. Repeated measurement across time points will be compared by mixed-effects regression models, including the interaction between time points and operation method and a random intercept for each patient. In addition, normality assumptions will be graphically assessed using quantile–quantile plots.

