## Background

Perforation of the gastrointestinal tract is the most common cause of secondary peritonitis [1, 2]. The underlying conditions may be appendicitis, anastomotic dehiscence, perforated diverticulitis, intestinal ischemia, or gastroduodenal ulcer, being the most common [3–7]. Faecal peritonitis is associated with high mortality and morbidity rate, with a reported 28-days mortality up to 20%, increasing to 32% at six-month follow-up [8]. Age, comorbidity, time to intervention, and the extent of peritonitis are important risk factors [7, 9–14]. A prerequisite for non-failure is sufficient source control, antibiotics, and in cases with organ dysfunction, postoperative intensive care treatment may be necessary [15–19]. Despite sufficient treatment, the risk of postoperative abdominal complications is high, and several patients may undergo a reoperation (s) to reveal and treat the complications. Another risk is the development of abdominal compartment syndrome. To manage this, three different strategies may be employed: a planned relaparotomy (PR), a relaparotomy on-demand (ROD), or the open abdomen (OA) principle [2, 5, 20–23]. A randomised controlled trial on PR versus ROD in patients with secondary peritonitis due to gastrointestinal perforation, including 232 patients, showed no significant difference in 1-year mortality (36% vs. 29%) and morbidity (44% vs. 40%) [20]. ROD resulted in significantly fewer relaparotomies and lower hospital-related healthcare costs.

A guideline [19] and consensus report [24] from the World Society of Emergency Surgery recommend ROD or VAC as the preferred treatment strategies for intra-abdominal infections with peritonitis and non-traumatic abdominal emergencies. The benefit of primary abdominal closure and ROD strategy is that patients do not require further scheduled operations. The risk is a delay in treatment for ongoing abdominal sepsis, other serious complications, and abdominal compartment syndrome, which may be difficult to recognise clinically in the severely ill patient [25–28]. Delays in treating severe complications might increase the risk of morbidity and mortality [9, 11, 14]. The advantages of VAC are a planned inspection of the abdominal cavity and the possibility to diagnose and treat potential or overt abnormalities on time. The risk is the development of enteroatmospheric fistula, difficulties in abdominal wound closure, and the development of an incisional hernia [29, 30].

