### Randomisation

Patients are included by a surgical equipoise followed by patient information and consent after recovery. The on-call surgeon will contact the primary investigator from each site when a patient is scheduled for diagnostic laparoscopy or explorative laparotomy on suspicion of secondary peritonitis. Patients fulfilling the inclusion criteria will be randomised after consent has been obtained by the surgical equipoise (Fig. 1). This could occur before, during, or at the end of index laparotomy, disclosing a complete overview of all potential candidates. Most patients will be able to receive both treatments regardless of what arm they are allocated without changing the treatment regimen. However, there will be some exceptions where it is necessary to modify or change the surgical treatment, irrespective of the randomisation allocation. Centres that do not receive approval from their respective scientific ethics committee to include patients through a surgical equipoise must obtain informed and written consent before randomisation. Randomisation will be web-based via (REDCap ®) in blocks of 2, 4, and 6 stratified for centre and age above or below 65 years. The justifications for stratifying according to the centre are that there might be differences in the surgical treatment, preoperative optimisation, and postoperative treatment, both in the ward and intensive care unit (ICU), which might affect the outcome. The patients will be randomised to either abdominal closure with ROD or open abdomen with VAC according to transparent reporting of trials (CONSORT) (Fig. 2). The randomisation tool and eligibility criteria can be accessed through our website, www.vacor.sdu.dk.

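### Randomisation is stratified by centre and age group, but the primary chi-square and its relative-risk interval ignore both: a mildly conservative analysis that gives away a little efficiency

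*Protocol article*

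**What the plan says.** - **Allocation** (Methods, Randomisation): patients are allocated "in blocks of 2, 4, and 6 stratified for centre and age above or below 65 years".
- **Reason for centre** (same section): "there might be differences in the surgical treatment, preoperative optimisation, and postoperative treatment" between centres, "which might affect the outcome".
- **Age as a risk factor** (Background): "Age, comorbidity, time to intervention, and the extent of peritonitis are important risk factors".
- **Primary analysis** (Methods, Statistical analysis): "The primary peritonitis-related complication outcome will be compared between intervention groups by the Chi-square test, reported as relative risk with a 95% CI". Neither stratification factor is mentioned.
- **Adjusted analysis** (same section): a separate logistic regression "adjusted for age, performance status, and comorbidity". Centre is not in the list, and no other analysis in the section names it.
- **Planning figures** (Sample size and power): complication rates of 40% with relaparotomy on-demand and 25% with VAC, with "the desired power of 80%, a significance level of 0.05, and an expected drop-out of 5%, a total of 340 patients should be included". Eight centres are active and two are in process.

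**The concern.** Blocked randomisation within centre and age group keeps the arms nearly balanced on those factors. If the factors predict the outcome, the treatment estimate varies less from trial to trial than under simple randomisation. The ordinary chi-square variance, and the usual standard error of the log relative risk, do not take credit for that reduction. The nominal 5% test then runs below 5%, the 95% interval covers more than 95%, and some power is lost.

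The protocol's own reasoning makes this relevant. It stratifies by centre because care may differ in ways that affect the result, and then leaves centre out of every analysis. A full protocol or analysis plan that is not shown might add detail. This is still not a gap left to such a document, because the article names the primary test and lists the covariates of the adjusted model.

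**Working it through.** **1. The plan's own figure.** Inputs: 40% vs 25%, 80% power, level 0.05 (two-sided assumed, as sidedness is not stated), 1:1 allocation (assumed), 5% drop-out.

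Pooled-variance formula, with mean rate 0.325:

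n per arm = [1.96·√(2·0.325·0.675) + 0.8416·√(0.40·0.60 + 0.25·0.75)]² / 0.15² = (1.298 + 0.550)² / 0.0225 ≈ 152.

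- Without continuity correction: 304 in total, and 304/0.95 = 320.
- With continuity correction: 165 per arm, 330 in total, and 330/0.95 = 348.

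The stated 340 lies between these. Evaluable patients: 340 × 0.95 = 323. Power of the ordinary test at 323 is 82.4% for a fixed design and 81.5% with four O'Brien–Fleming looks. The sample size is not in question here.

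**2. Size of the effect.** The documents give no centre or age effect, so these are assumed over a range.

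Simulation set-up: 20,000 trials per row, 323 patients, 10 centres × 2 age groups = 20 strata, near-exact balance within strata, overall rates calibrated to 40% and 25%. The between-centre SD and the age effect are set equal on the log-odds scale. The unadjusted chi-square is compared with the Cochran–Mantel–Haenszel (CMH) test. The usual log relative-risk standard error (SE) is compared with the Mantel–Haenszel (MH) SE. The level and power are for a single final test at 0.05.

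| Assumed effect | Level, chi-square | Level, CMH | Power, chi-square | Power, CMH | Power lost (points) | Width ratio, unadjusted/MH (null; alternative) |
|---|---|---|---|---|---|---|
| 0 | 5.2% | 5.1% | 82.4% | 82.1% | none | 0.999; 0.999 |
| 0.3 | 4.7% | 4.9% | 83.3% | 83.6% | 0.3 | 1.011; 1.008 |
| 0.5 | 4.3% | 5.0% | 84.0% | 85.2% | 1.2 | 1.030; 1.026 |
| 0.7 | 3.7% | 5.0% | 84.0% | 86.1% | 2.1 | 1.058; 1.049 |
| 1.0 | 3.0% | 5.0% | 85.0% | 89.4% | 4.4 | 1.107; 1.090 |

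Simulation error: √(0.05·0.95/20000) ≈ 0.15 points for the level and √(0.84·0.16/20000) ≈ 0.26 points for power.

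**3. Where the gain comes from.** Under the null at an effect of 0.5, the log relative risk has almost the same true spread whichever estimator is used (SD 0.1350 unadjusted, 0.1351 MH). The unadjusted SE averages 0.1378, so it is 0.1378/0.1350 = 1.021 times the true spread. At 0.3 the ratio is 0.1375/0.1370 = 1.004, and at 0.7 it is 0.1386/0.1326 = 1.045. The MH SE is about 1% below the true spread (0.1339/0.1351 = 0.991 at 0.5), so about one point of each width ratio is that shortfall. The estimate hardly changes; its stated uncertainty does.

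**4. Cross-check.** Two smaller simulations (6,000 trials each, centre SD 0.5, age odds ratio 2, 323 patients, 10 centres), one of them using actual blocks of 2, 4 and 6, gave chi-square levels of 4.3% and about 4.7%. Power was 83.2% vs 84.3% in one and 83.7% vs 85.3% in the other. Incomplete blocks loosen the balance a little, so the levels in the table are, if anything, at the conservative end.

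**5. First interim look.** 0.25 × 323 ≈ 81 patients in 20 strata is about 4 per stratum. At a nominal 0.05, CMH power was 29.2% against 29.9% for chi-square with centre SD 0.5 and age odds ratio 2. With no prognostic effect it was 28.4% against 31.2%. This matters little for stopping. The O'Brien–Fleming bound at that look is 2.024/√0.25 = 4.05, while the expected Z is 0.15/√(0.325·0.675·4/81) = 1.44. Crossing has a probability well under 1% with either test.

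**The case against.** The strongest reply is that nothing the protocol promises fails. The level is at or below nominal apart from simulation error, chi-square power stays above 80% in every row, and the lost power is surplus above the plan. The effect sizes are assumptions, and at the low end the loss is 0.3 points or nothing. Age, performance status and comorbidity are already in a supportive model. A 20-stratum analysis is not free when strata are sparse, as the first interim look shows. All of this stands. It limits the size of the point but does not remove the mismatch between design and primary analysis.

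Four stronger readings are tempting, and the documents do not support them.

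- **A reader might infer that the test is invalid or the trial underpowered.** The error is on the conservative side, and 323 evaluable patients still give more than 80% power.
- **A reader might infer that omitting centre makes the logistic model's interval too wide.** The too-wide argument applies to the primary relative-risk interval. In a logistic model, leaving out a prognostic factor pulls the odds ratio towards 1 and costs power.
- **A reader might expect gains of 4 to 6 points by also adjusting for preoperative SOFA.** Simulated gains of that size (84.5% to 88.4%, and 84.5% to 90.6% under stronger prognosis) come largely from SOFA. It is not a stratification factor, and with the same assumed prognosis, stratifying by centre and age alone gains about 1.2 to 2.8 points. SOFA adjustment is an optional extra, not part of this defect.
- **A reader might infer that adjusted and unadjusted results must be on different scales.** The protocol names no effect measure for the logistic analysis, and a relative risk can be derived from such a model.

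**Conclusion.** The point holds as a modest loss of efficiency. The protocol regards centre and age as possibly prognostic, randomises within them, and then fixes a primary test and interval that ignore them, with centre in no analysis at all.

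For assumed log-odds effects of 0.3 to 0.7, the actual level is about 4.7% to 3.7%, the interval is about 1% to 6% wider than the stratified one, and about 0.3 to 2 points of power are given up. At an effect of 1.0 the loss is about 4 points; at zero there is none. The direction is secure. The size rests on the assumed effects, on 10 centres with 20 strata, on 323 evaluable patients and on a two-sided 0.05 level. It is worth correcting because the correction is cheap, not because the conclusions would otherwise be unsafe.

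**What to change.** Before any comparison of the arms, including the first interim look:

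1. Make the primary analysis respect the stratification factors. Either use a CMH test with a Mantel–Haenszel relative risk by centre and age group, or a binomial or modified-Poisson model giving a marginal relative risk adjusted for centre and age. The protocol already plans binomial regression for relative risks on another outcome.
2. Fix a rule for pooling small centres, and state how it applies at the early looks, where strata are sparse.
3. Add centre to the adjusted model.
4. Keep the unadjusted chi-square and relative risk as a supporting analysis.

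The cost is wording only: centre and age group are known at randomisation, and no extra data or patients are needed. The downside is a small loss of power at sparse early looks if the factors turn out not to be prognostic, which pooling reduces.
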